#### Educational Workshop

The educational workshop is a 6-hour program that provides information about the etiology, biology, genetics, symptoms, and treatment of T2DM. Much of this material will be covered in the TC groups; however, the educational workshop was made available to those MFG family members who did not attend the TC sessions. It was conducted by the MFG clinician along with one of the authors (AK). They used the Spanish translation of the standardized videotape and coping skills guidelines developed by the author. The material is presented in basic, elementary school level Spanish with little use of idioms or colloquialisms. Presentations were made both visually and orally, including the use of role plays to allow family members with poor reading skills to adequately assimilate the material.

#### Ongoing MFG Sessions

Following the joining sessions and educational workshop, each cohort of 5-6 families met twice monthly for 3 months (6 sessions total). All sessions were co-led by the clinicians who conducted the 3 joining sessions. The first MFG session was focused on teaching problem-solving skills. Participants learned the mechanics of the problem-solving method and how to apply it to various problem situations. The method involves 7 steps as follows: define the problem, set goals, generate alternatives, evaluate each, select one, implement it, and evaluate outcomes. The subsequent 5 sessions were structured in the usual MFG fashion. This included a brief sharing period followed by group discussion. The discussion consisted of the sharing of personal experiences, identification of a problem situation, and the use of the problem-solving method to address the situation within the context of general group support. The group ended with review of the gains made by group members that week.

### Data Collection and Measures

Table 2 lists the measures to be used at each assessment point. Assessments were done at baseline and at 3, 6, and 12 months. In addition, the primary outcome variable (ie, diabetes self-management behaviors) was measured 6 weeks after the start of the first phase of the study to determine progress over time and the need for a change in treatment strategy. All measures were collected by a research assistant blind to the experimental conditions. Characteristics of the sample were measured at the initial visit including various demographic and clinical information.

The primary outcome is the difference in response scores of the SDSCA between the 4 groups at 3, 6, and 12 months after baseline [40]. The SDSCA is a well-validated instrument with excellent psychometric properties in several languages including Spanish [41,42]. It is the instrument most frequently used for assessing the acquisition of diabetes self-management behaviors [43]. The SDSCA is formatted to ask on how many of the previous 7 days the individual performed recommended self-management activities: eating healthy foods, following a diabetic diet, exercising, self-monitoring of glucose, and caring for one’s feet. A weekly self-care score ranging from 0 to 7 is generated, with higher scores corresponding to greater number of days carrying out the recommended behaviors.

Several secondary outcomes were also measured in this study. Diabetes self-efficacy, defined as the confidence of a person with diabetes to manage diet, exercise, track blood glucose levels, and overall control their diabetes, was measured using the 8-item Stanford Self-Efficacy Scale. Scores range from 1 (no confidence) to 10 (total confidence). The internal reliability of the Spanish language version of this measure is 0.85 [44]. Diabetes knowledge was measured using the Spoken Knowledge in Low Literacy Patients with Diabetes scale, a 10-item scale that assesses knowledge of glucose management, lifestyle modifications, recognition, and treatment of hyper- and hypoglycemia, and activities to prevent long-term consequences of the disease. Higher scores indicate better knowledge about diabetes, and the measure has been found to have excellent validity and reliability [45]. The patient’s degree of family support was measured using the 17-item Diabetes Family Support Behavior Checklist, which uses a 5-point Likert scale to assess the patients’ perceptions about their relatives’ support in medication taking, glucose monitoring, exercise, and diet [46]. Cronbach *α*s have been reported between 0.64 and 0.71 in Hispanic subjects with diabetes [26,47]. Collaborative goal setting was measured with the Spanish version of the Patient Assessment of Chronic Illness Care [48], a 20-item survey for evaluating the quality and patient-centeredness of chronic illness care received by the patient according to the Chronic Care Model paradigm [49]. The Spanish language translation of this instrument has demonstrated high reliability, internal consistency, and test-retest reliability [50]. Treatment session attendance was assessed for both patients and their relatives, and the percentage of treatment sessions attended by the key relative was used to analyze relationships with other outcomes. Glycemic control, defined as HgA1c level, was tested using a Bayer A1C NOW kit (Bayer Healthcare) using finger stick blood taken by a phlebotomist. Levels greater than 7.0% are considered poor glycemic control, and levels greater than 10.0% are considered uncontrolled diabetes [51]. Height, weight, BMI, and blood pressure were measured using standard procedures.

**Table 2 table2:** Study measures.

Variables	Measure	Content	Schedule^a^
Demographics	UCLA Client Data Inventory Cuellar acculturation scale Structured Clinical Interview for DSM-IV (SCID-I)	Age, gender, marital status, work status, educational level, acculturation level, and medical/psychiatric disorders	T1
Diabetes self-management	Revised Summary of Diabetes Self-Care Activities (SDSCA)	Assesses adherence to diet, exercise, self-monitoring, medications, and foot care	T1-T4 and week 6
Diabetes self-efficacy	Stanford Self-Efficacy Scale	Measures confidence to self-manage diabetes	T1-T4
Diabetes knowledge	Spoken Knowledge in Low Literacy Diabetes Patients (SKILLD)	Assesses knowledge of T2DM and its management	T1-T4
Family support	Diabetes Family Support Behavior Checklist	Assesses family support for T2DM self-management	T1-T4
Collaborative goal setting	Patient Assessment of Chronic Illness Care (PACIC)	Evaluates quality and patient centeredness of received treatment	T1-T4
Treatment attendance	Treatment Attendance Log	The percentage of sessions attended by patient/relative	T3
T2DM control	Bayer A1C NOW kit	Hemoglobin A1c level	T1-T4

^a^Data collection schedule: T1: baseline; T2: 3 months; T3: 6 months; T4: 12 months.

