### Hypothesis

There are 4 main hypotheses this study will test. First, subjects randomized to adaptive interventions that begin with nurse-led groups will show greater increases in diabetes self-management behaviors than those who begin with *promotore*-led groups. Second, among nonresponders to either of the first-line approaches, subjects randomized to a multifamily, problem-solving group will show greater improvements than those assigned to a single-family approach. Third, key relative’s participation in treatments will lead to (1) increased patients’ and relatives’ diabetes knowledge; (2) increased diabetes self-efficacy; (3) increased collaborative goal setting by families with health care providers; (4) increased family support; and (5) increased T2DM self-management behaviors. Fourth, subjects who are older, female, less educated, and less acculturated have an alcohol use or psychiatric disorder or have a longer history and greater severity of T2DM will (1) be less likely to have family members participate in treatment and (2) use diabetes self-management skills less often.

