## Methods

### Study Overview and Design

A sequential multiple assignment randomized trial study design evaluates 2 initial interventions for Hispanic adults with T2DM. Figure 1 indicates the study’s procedural flow. First, after baseline assessment, subjects were randomly assigned to receive the *Tomando control* (TC) intervention led either by a community health worker or *promotore* (TC-*promotore*) or by a nurse (TC-nurse). Both of these consist of 6 biweekly 2.5-hour group sessions. After the first 3 intervention sessions (phase 1), preliminary response was measured. Early responders to each intervention continued their same assigned intervention for 3 more sessions. For nonresponders (defined below), participants were rerandomized (phase 2) to receive either an augmented, stepped-up intervention that makes additional efforts to engage family members in the DSME enterprise for 3 more sessions or an MFG intervention designed to individually tailor treatment to address the obstacles encountered in promoting diabetes self-management behaviors. The MFG intervention consisted of 6 additional group sessions.

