### Initial Intervention: Tomando Control

The initial intervention, called “Taking Control of your Diabetes” or in Spanish “*Tomando Control de su diabetes*,” consisted of 6 biweekly sessions lasting 2.5 hours each led either by 2 trained *promotores* (*promotore*-led group) or by RNs (RN-led group). Each session included 10-12 patients. Patients’ families or friends were encouraged to attend sessions, which were held at Olive View-UCLA Medical Center. Each participant received a copy of the companion book, an audio relaxation tape, and an audio exercise tape with a booklet to supplement the material covered during the workshop sessions. The following topics were covered in sessions: (1) techniques to deal with the symptoms of diabetes and associated condition, (2) appropriate exercise, (3) healthy eating, (4) correct use of diabetes medications, and (5) working more effectively with health care providers in a collaborative partnership. Patients were expected to make weekly action plans, share experiences, and help each other solve problems they encountered in creating and carrying out their self-management strategies. The classes were highly participative and allowed participants to show mutual support and develop confidence in their abilities to manage their health. The program is based on the Stanford School of Medicine’s Chronic Disease Management Program developed by Lorig et al [36] and culturally adapted by Mauldon et al [37]. Similar program content was delivered in each group, with the only difference being the type of trainer: *promotore* versus RN.

Early response status was determined after the third TC session (ie, 6 weeks after starting the intervention). An independent evaluator blind to study condition used the Summary of Diabetes Self-Care Activities (SDSCA) to assess diabetes self-management behavior. A subject was considered an early responder if he/she showed a gain of 50% over baseline on the SDSCA. Early responders continued to receive the TC intervention that they were originally assigned. Nonresponders, those subjects who did not show a gain of 50% over baseline, were rerandomized to receive either the stepped-up, family-focused TC approach or the MFG. The following sections describe these 2 interventions.

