### Statistical Analysis

Data analysis will be conducted by intent-to-treat with participants analyzed according to their randomized intervention regardless of attendance. Our primary analytical tool will be the generalized linear mixed model (GLMM) [52,53]. GLMMs accommodate multiple outcome types in a unified framework via an appropriate link function (identity link for continuous normally distributed measures; logistic link for binary measures); allow for both fixed and time-varying covariates; automatically handle missing data, producing unbiased parameter estimates provided observations are missing at random; and appropriately account for the correlations induced by repeated measurements within subjects. We will fit GLMMs with fixed effects for the intercept, time (baseline, 3, 6, and 12 months), group, and a group-by-time interaction term, where the definition of group depends on the hypothesis and an unstructured covariance matrix. Model diagnostics will be used to determine suitability of more parsimonious (eg, autoregressive) correlation structures and nonlinear (eg, quadratic) effects for time. A sample size of 330 patients will provide 90% power to detect a difference of 0.29 in the score of SDSCA between the study groups. Subgroup analysis will be performed to determine if some moderators differentially affect the outcome such as patients’ age, gender, educational levels, duration of diabetes, and baseline HbA1c levels.

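### The primary outcome is a difference between four undefined groups that matches no hypothesis, and the stated model would not estimate it without bias because early responders are randomised only once

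*Protocol article*

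**What the plan says.** Study Overview and Design says that the trial "evaluates 2 initial interventions for Hispanic adults with T2DM": TC led by a nurse or by a promotore. Table 1 shows 165 patients in each arm. Response is assessed after the third session, at week 6, on the primary outcome instrument: "A subject was considered an early responder if he/she showed a gain of 50% over baseline on the SDSCA". For these patients there is no second randomisation: "Early responders to each intervention continued their same assigned intervention for 3 more sessions". The rest are randomised again: "Nonresponders, those subjects who did not show a gain of 50% over baseline, were rerandomized to receive either" the family-focused TC or the MFG. The ratio for this second randomisation is not given.

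Under Hypothesis, the first expectation is that "subjects randomized to adaptive interventions that begin with nurse-led groups will show greater increases in diabetes self-management behaviors" than those who start with a promotore. The second compares MFG with the single-family option and is confined to nonresponders. The third and fourth concern relatives' participation and patient characteristics.

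Data Collection and Measures then states: "The primary outcome is the difference in response scores of the SDSCA between the 4 groups at 3, 6, and 12 months after baseline".

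Statistical Analysis says: "Data analysis will be conducted by intent-to-treat with participants analyzed according to their randomized intervention regardless of attendance". Of the model it says: "We will fit GLMMs with fixed effects for the intercept, time (baseline, 3, 6, and 12 months), group, and a group-by-time interaction term". It adds that what counts as group changes with the hypothesis under test. It mentions no weighting, no replication of responders and no term for response status. It gives 330 patients and 90% power for an SDSCA difference of 0.29, without saying how many groups are compared.

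**The concern.** The design has six observed paths: responder, augmented TC and MFG, each under two leaders. It contains four adaptive interventions, each made of a starting leader plus one option for nonresponders. A responder has a first-stage assignment only and followed the rules of both interventions of that arm. Such a patient has no single place among four groups.

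The primary outcome is nevertheless worded as a four-group difference. The article's objective is to learn which sequence of strategies works best, so a reader will look to this endpoint for the answer. An analyst who follows the sentence literally must decide where the responders go. The choice changes what is estimated, and the stated model does not correct for it. Response is defined on an early SDSCA score, so responders and nonresponders are likely to differ on the later SDSCA even if no treatment has any effect.

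**Working it through.** **The plan's own figure.** With 165 per arm and two-sided 5%, 90% power for 0.29 requires SD = 0.29 / [(1.960 + 1.282) × √(2/165)] = 0.81. The article gives no SD, so the 90% can be neither confirmed nor refuted. At SD 1, power is 75% for a single visit, and 89.7% for the mean of three visits correlated at 0.5. The figure is therefore attainable for a two-group comparison under unstated assumptions. Nothing ties it to four groups.

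**Inputs not in the article, assumed here.** Response rate r of 20% to 60%; 1:1 rerandomisation; the gap G between responder and nonresponder means.

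**Reading A: the four embedded adaptive interventions, responders counted in both interventions of their arm, no weights.**
- The true responder share of each intervention is r. All responders but only half the nonresponders of an arm are observed under a given intervention, so the unweighted share is s = r / [r + (1 − r)/2] = 2r/(1 + r).
- Bias in each mean is (s − r) × G.
- The MFG versus augmented-TC contrast within a leader is multiplied by (1 − s)/(1 − r) = 1/(1 + r).

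| r | unweighted responder share | bias in mean per 1-point gap | contrast retained |
|---|---|---|---|
| 20% | 33% | 0.13 | 83% |
| 30% | 46% | 0.16 | 77% |
| 40% | 57% | 0.17 | 71% |
| 50% | 67% | 0.17 | 67% |
| 60% | 75% | 0.15 | 63% |

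A simulation of 2,000,000 patients with 34% response agrees. With no treatment effect, all four unweighted means are about 0.13 too high; weighted 1 (responders) to 2 (nonresponders), they are 0.00. With a true MFG effect of 0.29 among nonresponders, the within-leader contrast is 0.19 weighted and 0.14 unweighted.

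Between leaders the error can be small. With response of 50% versus 30%, a 1-point gap and no other difference, the true contrast is 0.20 and the unweighted one is 0.667 − 0.462 = 0.205.

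**Reading B: four treatments (TC-nurse, TC-promotore, augmented TC, MFG).** The first two groups hold only responders, the last two only nonresponders. In the simulation with no treatment effect (outcome SD 0.81; correlation with the response score 0.48/0.81, about 0.59), the means are 0.51 and −0.27. The difference of 0.78 arises from selection alone and exceeds the 0.29 in the power statement.

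**Reading C: four nonresponder cells (leader by second-stage option).** MFG versus augmented TC within a leader remains a randomised contrast. Nurse versus promotore does not, because each side is selected by a result observed after randomisation. In a simulation where the nurse arm raises early response from 34% to 50% and does nothing to the final outcome, nurse minus promotore among nonresponders is −0.11 instead of 0. Each cell holds 330(1 − r)/4 patients: 66 at r = 20% and 33 at r = 60%. At SD 0.81, power for 0.29 is then 54% and 30%.

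**The two hypotheses.** In the same null simulations, the first-stage contrast on everyone and MFG versus augmented TC among nonresponders both come out at 0.00. With the MFG effect set to 0.29, the nonresponder contrast returns 0.29.

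**The case against.** The strongest reply is that Statistical Analysis lets the definition of group follow the hypothesis. Under the first hypothesis, group is the starting leader; under the second, it is the second-stage option among nonresponders. Both are randomised contrasts that the mixed model handles without weights, and the Discussion presents these as the trial's questions. On this view the four groups may be loose wording for the two pairs. This stands as a defence of the hypothesis tests. It does not cover the primary outcome sentence, since no hypothesis supplies a four-level group.

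Second, an article condenses a fuller plan, and weighting may be set out there. That also stands: the article nowhere says that the analysis is unweighted, and silence does not prove it. What is fixed here, though, is the endpoint itself. A fuller plan would have to redefine that endpoint as well as add technique. Figure 1 was not available for this check and may label the groups, but none of the three labellings worked through above rescues the contrast under the stated model.

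Third, a reader might infer that responders are to be dropped from the nurse versus promotore comparison. The article does not say so. All 330 patients have a first-stage assignment, and the intent-to-treat statement points to keeping them. Only the second hypothesis is restricted to nonresponders, and there the restriction is correct.

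**Conclusion.** The concern holds for the primary outcome as worded, and only for that. The four groups are undefined, correspond to no stated hypothesis, and under any of the three readings examined do not form a fully randomised contrast that the stated model estimates without bias.

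The size depends on the reading. Under unweighted pooling, the MFG versus augmented-TC contrast retains 83% to 63% of its true value for response rates of 20% to 60%. This assumes 1:1 rerandomisation; neither the rates nor the ratio is in the article. The 0.78 and −0.11 under the other two readings are illustrations from one assumed correlation and SD.

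Two stronger conclusions may tempt a reader and are not supported. The trial's hypothesis tests are not shown to be biased: leader on all 330 and second-stage option among nonresponders are unaffected. Nor does unweighted pooling create a false positive within a leader; the error there is attenuation toward zero.

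**What to change.** Bring the primary outcome sentence into line with Hypothesis and Statistical Analysis. Name two primary contrasts: first-stage arm on all 330 patients, and second-stage arm among the rerandomized nonresponders. State the second-stage allocation ratio.

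If the four embedded adaptive interventions are also to be compared, define them explicitly and use an estimator made for this design. Replicate each responder to both interventions of the arm and weight every record by the inverse of its actual randomisation probability. If both stages were 1:1, this is 1/0.5 = 2 for responders and 1/(0.5 × 0.5) = 4 for nonresponders. Use robust standard errors clustered on patient.

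The change affects wording and code and needs no new data. The weighted comparison will have somewhat wider intervals. The second contrast rests on fewer patients than the power statement covers: 330(1 − r)/2 per option, that is 132 at 20% response and 66 at 60%, with power for 0.29 of about 83% and 54% at SD 0.81. That limit is already in the design, and naming the contrast makes it visible.

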### Second Intervention: Family-Focused TC Approach

For those subjects who were randomly assigned to receive the augmented TC, the TC clinician (either a *promotore* or nurse, depending on the original group assignment) conducted up to 3 home visits that were designed to explain the purpose of the TC intervention to a key relative so as to reengage the family member in the group process. Each visit was carefully scripted to address the family’s role in helping the family member with diabetes. The first home visit was focused on the family’s reaction to having a loved one with diabetes and was designed to elicit how the family functioning had changed since the diagnosis was made. The second session aimed to help the family set realistic goals for participation in TC including the length of the groups and the expectations of the family in using the material covered in the group to effect behavior change. Logistical details (eg, which family member would accompany the patient to the group, how they would get to the group, and so on) were identified and obstacles to attendance were resolved. The third session solidified the gains made in the first 2 sessions as well as emphasized to the family that the *promotore* or nurse was available for crises or problem resolution if last-minute difficulties arose prior to the TC group. These engagement strategies have been very effective in increasing the participation of family members in group therapy [38].

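### The third hypothesis makes a causal claim from key-relative attendance pooled over treatment paths, and that attendance is partly a result of early SDSCA change

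*Protocol article*

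**What the plan says.** The third hypothesis (Hypothesis section) is worded causally: "key relative’s participation in treatments will lead to" gains in knowledge, self-efficacy, collaborative goal setting, family support and self-management behaviour. The exposure is given in Data Collection and Measures: "the percentage of treatment sessions attended by the key relative was used to analyze relationships with other outcomes". Table 2 describes it as "The percentage of sessions attended by patient/relative" and schedules it at T3, which is 6 months.

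What a relative can attend depends on the week-6 result. Under Initial Intervention: Tomando Control (TC), "A subject was considered an early responder if he/she showed a gain of 50% over baseline on the SDSCA". Three paths follow:

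- **Responders:** "Early responders to each intervention continued their same assigned intervention for 3 more sessions".
- **Nonresponders, augmented TC:** three more sessions, and the clinician "conducted up to 3 home visits that were designed to explain the purpose of the TC intervention to a key relative". The same section says that such strategies work well to raise family participation.
- **Nonresponders, multifamily group (MFG):** three joining sessions with each family, a workshop and group sessions ("The MFG intervention consisted of 6 additional group sessions"). The workshop was offered to relatives who had not been at the TC sessions.

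**The concern.** Nobody is randomised to have a relative attend, so a causal reading already depends on confounders being controlled. The design adds a second problem. The SDSCA gain at week 6 decides who receives the contacts built to draw relatives in, and SDSCA gain is also the fifth outcome of the hypothesis. Patients with little early gain are steered towards higher relative attendance. If all paths are pooled, high attendance partly marks a poor early course, and a real benefit of participation could look like no benefit or harm.

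Time order is the other weakness. One 6-month percentage cannot be a cause of a 3-month outcome to the extent that it counts later sessions.

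**Working it through.** The article gives no figure for this hypothesis, so there is none to reproduce. Its one power statement concerns the comparison of study groups.

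**1. Contacts on offer, from the intervention sections**

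| Path | Group sessions only | All contacts counted |
|---|---|---|
| Responder | 3 + 3 = 6 | 6 |
| Augmented TC | 3 + 3 = 6 | 6 + up to 3 visits = up to 9 |
| MFG | 3 + 6 = 9 | 9 + 3 joining + 1 workshop = up to 13 |

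The article does not say which contacts count as sessions, so both columns are carried forward.

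**2. Time order.** Rerandomisation follows the week-6 assessment, about 1.5 months in. Six MFG sessions at two a month, starting at once with no time for joining sessions or workshop, would fall at about 1.5, 2, 2.5, 3, 3.5 and 4 months. At least two fall after an on-time 3-month assessment, and more if the joining sessions take time.

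**3. Bias of a pooled slope.** Let A be the proportion attended, R early response, p the response rate, L the responders' lead in SDSCA change, D the mean attendance of responders minus that of nonresponders, V the variance of A, and β the true slope. If the outcome is βA + LR + error, then

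pooled slope = β + L × p(1 − p) × D / V.

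Session counts enter only through D and V. If D = 0 there is no bias, whatever the denominators.

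**4. Numbers, all contacts counted.** Assumptions, none from the article: p = 0.40, 50% attendance at group sessions and workshop on every path, 90% at home visits and joining sessions, residual SD 0.8.

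- Augmented TC: (6 × 0.5 + 3 × 0.9)/9 = 0.633. MFG: (9 × 0.5 + 3 × 0.9 + 0.5)/13 = 0.592. Responders: 0.50.
- D = 0.50 − (0.633 + 0.592)/2 = −0.113, and p(1 − p)D = 0.24 × (−0.113) = −0.0271.

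A simulation of trials of 330 patients (400 replicates), with true slope +0.30, gave:

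| Responder lead L (points) | Mean pooled slope | Trials with a negative slope |
|---|---|---|
| 0.5 | +0.01 | 49% |
| 1.0 | −0.27 | 85% |
| 1.5 | −0.54 | 98% |

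The first row implies V = 0.0271 × 0.5/0.29 = 0.047, an attendance SD of about 0.22. Put back into the formula, this gives 0.30 − 0.58 = −0.28 and 0.30 − 0.87 = −0.57 for the other rows, within 0.03 of the simulation. The sign turns at L = 0.30/0.58 = 0.52 points. For a true slope of 0.60 it turns at 0.60/0.58 = 1.03 points. With a true slope of 0, the simulated slope was −0.28 to −0.89. A lower response rate shrinks the bias: at p = 0.20 the factor p(1 − p) is 0.16 instead of 0.24, about two thirds, if D and V stay the same.

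**5. Group sessions only**, true slope +0.30, leads of 0.5, 1.0 and 1.5:

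- Equal attendance on all paths: about +0.29 throughout, although the denominators are 6, 6 and 9.
- Nonresponders' second-stage attendance 15 points higher: +0.12, −0.07, −0.21.
- 30 points higher: −0.04, −0.37, −0.72.

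**6. Change versus level.** Nonresponse means too small a relative gain, not poor self-care. On a 0 to 7 score, anyone starting above 7/1.5 = 4.67 cannot respond. A simulation of the 50% rule itself with no participation effect (inputs assumed) gave a pooled slope for SDSCA change of −0.67 to −0.85 points with all contacts counted, and −0.21 to −0.33 with group sessions only. For SDSCA level it was −0.14 to +0.01. A separate set of runs (baseline mean 2.5 to 4.0, SD 0.8 to 1.2) put the level slope at −0.24 to +0.08 SD.

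**7. Remedies tried.** Attendance at the first three TC sessions gave a slope within about 0.015 of zero when there was no true effect. Adjusting for early response and second-stage arm recovered true slopes of 0, 0.30 and 0.60.

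**The case against.** The strongest reply is that no model for this hypothesis is stated. The measures section speaks only of relationships, and Statistical Analysis leaves the definition of group to the hypothesis and allows covariates. An analysis adjusted for response and arm would remove the path-related bias, and that detail may be in a document not shown. This stands: the article does not commit to an unadjusted pooled slope. What remains is what it does fix, namely a causal hypothesis, one non-randomised percentage as its exposure, and one recording point at 6 months.

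Other objections also stand:

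- Totals of 9 and 13 hold only if visits, joining sessions and workshop count as sessions, and the workshop was meant for relatives who had missed TC.
- T3 may simply be when a running log is summarised. It does not prove that 3-month outcomes will be related to later sessions, and the 12-month outcomes come after the interventions.
- Attendance at the first three sessions alone leaves out the family-targeted contacts that the hypothesis is largely about.

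The reply that unequal denominators are harmless in themselves is correct, as step 5 shows. It does not remove the concern, because equal attendance on all paths would mean that the engagement contacts had failed.

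**Conclusion.** The point holds for SDSCA change, the fifth outcome of the hypothesis. A percentage pooled over paths is partly a consequence of early SDSCA change, and for MFG it includes sessions after the 3-month outcome. Under the assumed inputs the association is pulled downward and its sign can reverse: a true +0.30 becomes +0.01 to −0.54 with all contacts counted, and +0.12 to −0.72 with group sessions only and a 15 to 30 point attendance gap. Response rate, attendance levels and responder lead are all assumed, so these are illustrations and not estimates for this trial.

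A reader might infer more than the article supports:

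- **That the sign will be wrong.** Reversal is conditional. With a true slope of 0.60 it needs larger leads or attendance gaps.
- **That unequal session counts cause the bias.** They do not; the attendance level does.
- **That poor self-management triggers the extra contacts.** The trigger is a gain below 50%, and for SDSCA level the bias was small in these runs. It depends on how baseline scores are spread and persist.
- **That all five outcomes are shown to be biased.** For the other four it depends on how closely they track early SDSCA response, which is not given. Lack of randomisation and, for MFG, time order do affect all five.

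The change is worth making: this is one of four main hypotheses, though not a randomised comparison.

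**What to change.** 1. State which contacts count as sessions.
2. Do not relate a percentage pooled over all paths to outcomes.
3. Relate key-relative attendance at the three TC sessions before week 6, which are common to all 330 patients, to the 3-, 6- and 12-month outcomes. Adjust for first-stage arm, baseline outcome and the baseline predictors in the fourth hypothesis. Do not adjust this analysis for week-6 response, which comes after the exposure.
4. Analyse second-stage attendance within response-by-arm path, or adjusted for response and second-stage arm. Adjust for first-stage attendance and use only outcomes measured after the sessions counted.
5. Report the third hypothesis as an association instead of "participation in treatments will lead to".

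No new data are needed if the attendance log records individual sessions; the rest is analysis and wording. The cost is in information. The early exposure takes only the values 0 to 3 and omits the family-targeted contacts, within-path estimates are less precise, and unmeasured family engagement may still confound both analyses.
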